**Protocol synopsis**

| Study Drug | Anlotinib hydrochloride capsule |
| --- | --- |
| Protocol Title | A phase III multi-center, randomized, double-blind, parallel controlled trial of anlotinib plus gefitinib versus placebo plus gefitinib as first-line therapy in stage IIIB-IV EGFR-mutated non-small cell lung cancer (NSCLC) |
| Protocol Number | FL-ALTER |
| Version Number | 1.6 |
| Version Date | October 29, 2021 |
| Sponsor | Sun Yat-sen University Cancer Center |
| Study Design | A multi-center, randomized, double-blind, placebo-controlled parallel study |
| Study Nature | An investigator-initiated clinical study |
| Study Population | Treat-naive patients with stage IIIB-IV EGFR-mutated NSCLC |
| Sample Size | A total of 310 patients were randomized in a 1:1 ratio to the experimental group and the control group. |
| Objective | To observe and evaluate the efficacy and safety of anlotinib combined with gefitinib in patients with advanced EGFR-mutated NSCLC. |

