| Study Procedures | Group A (experimental group): 250 mg gefitinib, po, qd + 12 mg anlotinib hydrochloride capsule, po, qd, D1-D14; administered under fasting conditions (administration of the two drugs at the same time every day), every 3 weeks;  Group B (control group): 250 mg gefitinib, po, qd + anlotinib hydrochloride placebo, 1 tablet, po, qd, D1-D14; administration of the two drugs at the same time every day taking medication at the same time every day), every 3 weeks.  Drugs will be administered every 21 days until disease progression, intolerable toxicity, withdrawal of consent, or drug discontinuation according to the investigator's judgment. |
| Endpoints | Efficacy is evaluated every 2 cycles (6 weeks) after enrollment and every 3 cycles (9 weeks, 63±7 days) from 27 cycles using RECIST 1.1 criteria;  **Primary Endpoints:**  Progression-free survival (PFS)  **Secondary Endpoints:**  1. Overall Survival (OS)  2. Overall Response Rate (ORR)  3. Disease control rate (DCR)  4. Time to disease progression (TTPD)  5. Duration of Response (DoR)  6. Quality of life score (QoL) |
| Safety | Any adverse events (AEs) that occurred in all subjects during the clinical study period will be observed, including abnormal clinical symptoms and vital signs, and abnormalities in laboratory tests. The clinical characteristics, severity, time of occurrence, duration, treatment methods, and prognosis of adverse events will be recorded; meanwhile, the correlation between adverse events and the study drugs will be determined. The safety of drugs is evaluated according to National Cancer Institute's Common Terminology Criteria for Adverse Events (NCI-CTC AE) version 4.0. |
| Exploratory Study | The mechanism of drug resistance will be monitored by next-generation sequencing (NGS) before treatment, at the first efficacy evaluation, and during tumor progression. |

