| Statistical Analysis | **Efficacy analysis**  For the PFS (primary endpoint), the median value and 95% confidence interval (CI) are estimated and survival curves are obtained using the Kaplan-Meier method. Survival differences between the two groups are estimated by log-rank tests. COX regression analysis is used to compare the survival between the two groups after adjusting for stratification factors such as EGFR mutation site, gender, PS score, and pathological type; the hazard ratio (HR) and 95% CI after adjusting for the above stratification factors are calculated.  For the secondary endpoints, such as OS, TTPD, and DoR, the median value and 95% CI are estimated and survival curves are obtained using the Kaplan-Meier method. The log-rank test is used to compare the survival between the two groups; DCR and ORR with 95% CI are calculated, and comparisons between treatment groups are performed using a Cochran-Mantel-Haenszel (CMH) test or chi-square test. Two independent samples will be compared for the differences between the two groups in QoL scores by the t-test or Wilcoxon rank sum test.  **Safety** **analysis**  Descriptive statistical analysis is mainly used, and the mean or incidence of examination results before and after administration could be compared if necessary. Vital signs, physical examination, and laboratory tests mainly describe the changes before and after treatment and the relationship between abnormal changes and study drugs. All AEs are standardized by MedDRA code, and the incidences of AEs and grade 3 or above AEs are summarized and compared between the two groups according to system organ class (SOC) and preferred language (PT) in MedDRA code and CTCAE classification. The AEs and serious AEs occurred in this study are also summarized in the table. |
| Prespecified Efficacy Analysis | An Independent Data Monitoring Committee (IDMC) will be established to conduct 1-2 interim analyses to provide further recommendations and to ensure the safety of subjects.  Final analysis: It is performed when approximately 192 PFS events have occurred |
| Study Schedule | Enrollment date of the first subject: January 2019  Enrollment date of the last subject estimated: June 2021  Estimated date of the end of the study: December 2022 |

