**Table 6.1.1 Drug Information**

| **Drugs** | **Specification** | **Drug storage** | **Manufacturer** |
| --- | --- | --- | --- |
| Anlotinib | 12 mg/tablet  10 mg/tablet  8 mg/tablet | Store in a sealed and dark place below 25°C | Chia Tai Tianqing Pharmaceutical Group Co., Ltd. |
| Placebo | 0 mg/tablet | Store in a sealed and dark place below 25°C | Chia Tai Tianqing Pharmaceutical Group Co., Ltd. |
| Gefitinib | 250 mg/tablet | Store at a room temperature of 15-30°C | Chia Tai Tianqing Pharmaceutical Group Co., Ltd.  Astrazeneca Pharmaceuticals Co., Ltd. |

Anlotinib and placebo are produced by Chia Tai Tianqing Pharmaceutical Group Co., Ltd., and batch numbers and expiration dates are detailed in the drug test report. Gefitinib tablets are produced by Chia Tai Tianqing Pharmaceutical Group Co., Ltd. or purchased from Astrazeneca Pharmaceuticals Co., Ltd.

- - 1. **Drug packaging**

Anlotinib is packaged in capsules, with 7 tablets per plate and 2 plates per small box.

- 1. **Dose and administration regimens**

Group A (experimental group): 250 mg gefitinib, po, qd + 12 mg anlotinib hydrochloride capsule, po, qd, D1-D14; administered under fasting conditions (taking medication at the same time every day), every 3 weeks;

Group B (control group): 250 mg gefitinib, po, qd + anlotinib hydrochloride mock capsule, 1 tablet, po, qd, D1-D14; administered under fasting conditions (taking medication at the same time every day), every 3 weeks.

Anlotinib is given at a dose of 12 mg as the initial dose (po, qd, D1-D14) every 21 days and the drug combination is used until disease progression, intolerable toxicity, withdrawal of consent, or drug discontinuation according to the investigator's judgment. If the administration is suspended due to no recovery of drug toxicity, treatment cycle is recalculated according to the regimen of consecutive 2 weeks and stop 1 week, while the follow-up period is still calculated according to the screening date. If patients discontinue anlotinib due to intolerable toxicity, gefitinib can be continued until disease progression.

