The investigator may destroy the used study drugs (non-state controlled chemicals) and empty boxes/bottles after written notification to the co-organizer without endangering the health of the population. The investigator should keep all study drug-handling records.

These records must document the evidence and quantity of each batch of destroyed drugs, disposal methods (as required by local law), and the person who handled the study drugs.

1. Dose Adjustment and Discontinuation
   1. **Dose adjustment of anlotinib**

The initial dose of anlotinib or placebo is 12 mg/day, and the anlotinib dose can be reduced to 10 mg/day for the first dose and 8 mg/day for the second dose. For patients unable to tolerate a dose of 8 mg/day, anlotinib should be discontinued and gefitinib should be administered alone until PD or intolerable toxicity.

|  | **Study group (anlotinib)** | **Control group (placebo)** |
| --- | --- | --- |
| Initial dose | ■■ 12 mg/day, qd | □□ 12 mg/day, qd |
| First dose reduction | ● 10 mg/day, qd | ○ 10 mg/day, qd |
| Second dose reduction | ■ 8 mg/day, qd | □ 8mg/day, qd |
| Third dose reduction | Discontinuation | Discontinuation |

- 1. **Dosage suspension and reduction**

If dosage suspension caused by drug toxicity has not recovered, the duration of dosage suspension should not exceed 6 weeks per cycle. Follow-up visits will be conducted at least every 1-2 weeks during discontinuation and the drug will be restarted at the original dose or a lower dose level after recovery of toxicity.

The subjects cannot return to the previous dosing pattern after dosage reduction and a maximum of three dose reductions are allowed in anlotinib therapy.

When patients experienced grade 3 hematological toxicities and grade 2 non-hematological toxicities, dosage suspension and reduction are considered; Dosage suspension will be performed in non-hematological toxicities including controllable nausea, vomiting, and fever with a definite cause (below 38°C) until the toxicity became tolerable. Aggressive symptomatic management without dosage suspension and reduction can also be conducted.

- - 1. **Standardization of dose suspension and reduction**

To ensure consistency of dosage adjustment, dosage suspension is performed at the time of dosage adjustments for each cycle. The criteria of dose suspension and reduction are as follows (once the criteria of dosage reduction are met which is considered poorly tolerated, a reduction should be performed).

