**Table 7.4.3. Proteinuria classification criteria (NCI-CTC AE 4.0) and recommendations for prevention and treatment**

| Criteria | Definition | Prevention and treatment |
| --- | --- | --- |
| Grade 1 | Urokinase protein (+) or 24-hour urine protein excretion <1.0 g | Continuing anlotinib administration without dose adjustment |
| Grade 2 | Urokinase protein (++) or 24-hour urine protein excretion of 1.0-3.4 g | Continuing anlotinib administration without dose adjustment; Drug intervention should be considered; Monitor 24-hour urine routine and 24-hour urine protein excretion |
| Grade 3 | 24-hour urine protein excretion >3.4 g | Suspension of anlotinib; Consultation with a nephrologist specialist; Drug intervention should be performed; Dose reduction of anlotinib after recovery of proteinuria to ≤ grade 2; If grade 3 proteinuria still occurs after 2 dose reductions, anlotinib therapy should be permanently discontinued |

1. **Bleeding**

The PT and international normalized ratio (INR) should be closely monitored during the administration of anlotinib to monitor patients for bleeding tendencies and related symptoms; the drug should be interrupted if a grade 3-4 bleeding event occurs. If [upper gastrointestinal bleeding](https://www.sciencedirect.com/science/article/pii/S0025712508000023) occurs, anlotinib must be interrupted and aggressively treated according to clinical protocols should be performed.

1. **Thrombus**

If any arterial thrombosis (e.g., cerebral ischemia, stroke, angina, myocardial infarction) occurs, drug administration should be discontinued immediately and the study should be withdrawn. If symptomatic grade IV venous thrombosis occurs, drug administration should be discontinued in patients, with withdrawal from the study.

For patients with thrombotic symptoms, symptomatic treatment, surgery, or anticoagulant drugs should be scheduled immediately.

For patients with venous thrombosis, the criteria for dose adjustment are as follows:

| **Venous thrombosis** | **Dose adjustment** |
| --- | --- |
| Grade II | Anlotinib is maintained at the original dose level and closely monitored. |

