- The target lesion identified at baseline should be examined under the same conditions as the baseline examination (layer thickness of the scan, use of contrast agent, etc.); Patients with bone metastases detected at baseline should be examined again and other lesions other than the above or new lesions suspected should also be detected.
- Unscheduled imaging may be performed when disease progression is suspected (e.g., worsening of symptoms) or when confirmation of PR or CR is required (6 weeks after achieved PR or CR);

1. QoL: Conducting by the investigator asking questions and the subject answering;
2. ECOG PS;
3. AEs: Recording AEs from the date of the first dose of the study drug to at least 30 days after the last dose and follow up until the AEs resolved or stabilized;
4. Concomitant medications: Concomitant medications and therapy during the trial should be recorded and if the subject discontinues treatment, the concomitant medication and therapy are recorded only in the case of a novel or unresolved AEs associated with treatment;
5. Study drug: Distribution and recovery of study drug.
   1. **End-of-treatment and withdrawal study**

At the end-of-treatment and withdrawal study, if the patient is not examined within 14 days before the end of treatment, the following tests should be performed.

1. ECOG PS;
2. Vital signs: Heart rate, respiratory rate, temperature, and BP;
3. Physical examination: Facial features, integumentary system, lymph nodes, eyes, ears, nose, throat, oral, respiratory system, cardiovascular system, abdomen, urinary tract system, musculoskeletal system, nervous system, and spiritual state;
4. BP monitoring: BP is measured by the investigator, coffee and tobacco intake are prohibited within 30 minutes before each BP is measured and the measurement is taken in the sitting position with the arm at heart level after at least 10 minutes of quiet sitting, and each BP measurement is taken on the same side;
5. Hemanalysis: Hemoglobin, red blood cell, white blood cells, absolute neutrophil count, lymphocyte count, and platelet count;
6. Urinalysis: Urine protein, glucose, occult blood (red blood cell and white blood cell), pH, and ketone bodies; If the semi-quantitative method shows the levels of protein ≥ 2+ (e.g., urine test strip), 24-hour urine analysis is performed;

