The SS population will serve as the population for the safety analysis. All randomized subjects have received at least one dose of the research drug and have a post-administration safety record.

- - 1. **Statistical analysis plans**

All statistical analysis will be performed using the SAS statistical package (≥9.3 version) with a two-sided test. P ≤0.05 is considered significant, with 95% confidence intervals (CI).

1. Baseline

Quantitative data including age, height, weight, and so on are described as mean ± standard deviation (SD), median, maximum, and minimum values, and qualitative data such as gender and ECOG score are reported by number and frequency.

1. Efficacy assessment

The primary endpoint of this trial, PFS, will be estimated using the Kaplan-Meier method with a 95% CI and presented with the Kaplan-Meier curve. The comparison of PFS between intervention arms will be performed using a stratified log-rank test. The HR and the corresponding 95% CI will also be provided based on a Cox proportional hazard model, using such as age, ECOG PS, and EGFR mutations (exon 19 deletions or an exon 21 mutation) as stratification factors.

The secondary endpoint such as OS, TTPD, and DoR will be analyzed in the same method as the primary endpoint. The cochran-mantel-haenszel (CMH) method or Chi-square test will be used to compare ORR and DCR between the groups, and Fisher's exact test method will be used to calculate ORR, DCR, and 95% CI. The Student t-test or Wilcoxon rank sum test will be used to compare the QoL between the groups.

1. Safety analysis

Safety analysis will be mainly descriptively summarized and the mean or incidence of pre- and post-administration examination tests (if necessary). Vital signs, physical examination, and laboratory tests will be demonstrated mainly through the changes from baseline in clinical and the incidence of abnormalities. All AEs will be coded using the Medical Dictionary for Regulatory Affairs (MedDRA) for safety analysis. Summary and compare the incidence of all AEs, treatment-emergent adverse events (TEAEs) with grade 3 or more, serious TEAEs, and so on between two intervention arms will be tabulated according to MedDRA PT and primary system organ class (SOC), as well as CTCAE grading.

- 1. **Interim analysis**

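### Crude AE incidence is compared between arms although AE recording follows treatment; if PFS is 15 vs 10 months, longer observation alone could add about 2 to 8 points for accumulating AEs

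*Protocol*

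**What the plan says.** - **Measure.** Section 13.2, Safety analysis, sets out to "Summary and compare the incidence of all AEs, treatment-emergent adverse events (TEAEs) with grade 3 or more, serious TEAEs" and similar categories between arms. The synopsis says the same: "the incidences of AEs and grade 3 or above AEs are summarized and compared between the two groups". Section 10.2, on causality, uses the number of subjects in the safety set as the denominator for drug-related AEs, so incidence there is per subject and not per unit of time.
- **Length of observation.** Section 9.2 calls for "Recording AEs from the date of the first dose of the study drug to at least 30 days after the last dose". The synopsis fixes dosing: "Drugs will be administered every 21 days until disease progression, intolerable toxicity, withdrawal of consent, or drug discontinuation" at the investigator's judgment.
- **Expected difference.** Section 3.3 assumes median PFS of 15 months on anlotinib plus gefitinib and 10 months on placebo plus gefitinib.
- **Stopping anlotinib.** Section 6.2: "If patients discontinue anlotinib due to intolerable toxicity, gefitinib can be continued until disease progression". Section 7.1, for patients who cannot tolerate 8 mg/day: "anlotinib should be discontinued and gefitinib should be administered alone until PD or intolerable toxicity". Some events end participation altogether; for arterial thrombosis, section 7.4 says "drug administration should be discontinued immediately and the study should be withdrawn".
- **Which drug is the study drug.** The synopsis has "Study Drug | Anlotinib hydrochloride capsule" and nothing else under that label, while Table 6.1.1 in section 6 also lists gefitinib.
- **Status.** Section 13.2 describes the safety analysis as mainly descriptive.

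**The concern.** A per-subject incidence counts whether a patient had an event at any time while observed. If one arm is observed longer, more of its patients reach a first event even when the monthly risk is the same. The design expects the anlotinib arm to stay on treatment longer, so part of any crude excess could be the price of longer disease control and not of toxicity. Stops for toxicity pull the other way wherever they also end AE recording.

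This matters only for events that keep accumulating. Table 3 of the protocol (anlotinib 12 mg alone, 21 patients) suggests that some do: grade III AEs rose from 2/21 in the first two cycles to 7/21 over the whole study. Any grade I/II AE was already 21/21 in the first two cycles, so longer observation could add nothing there.

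Safety is part of the stated objective. What is at stake is how a reader interprets the tables for grade 3 or higher AEs, serious AEs and other accumulating events.

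**Working it through.** **1. The plan's own figures.** Section 3.3 gives medians of 15 and 10 months, two-sided alpha 0.05, 80% power, 18 months' accrual and 18 months' follow-up.
- Schoenfeld events: 4 × (1.960 + 0.842)² / (ln 1.5)² = 191, against 192 stated.
- With exponential PFS, uniform accrual and 124 per arm, expected events are 124 × 0.704 = 87.4 and 124 × 0.836 = 103.7, against 88 and 104 stated.
- 124 / 0.80 = 155 per arm, 310 in all, as stated.

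The same medians and calendar are used below.

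**2. Length of the AE window.** Assumptions: time on treatment T is exponential with hazard μ = ln 2/15 = 0.0462 (anlotinib) or ln 2/10 = 0.0693 (control) per month; data cut-off C is uniform on 18 to 36 months; the window is W = min(T + 1, C); there is no dropout and no extra toxicity stop.

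E[W] = 1 + (1/μ) × {1 − [exp(−17μ) − exp(−35μ)]/(18μ)}

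- Control: 1 + 14.43 × (1 − 0.176) = 12.9 months.
- Anlotinib: 1 + 21.64 × (1 − 0.310) = 15.9 months.

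**3. Crude incidence at equal monthly AE rates.** With constant AE hazard λ in both arms, and s = μ + λ:

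P(at least one AE) = 1 − exp(−λ) × (μ + λA)/s, where A = [exp(−17s) − exp(−35s)]/(18s)

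The protocol gives no λ, so it is solved for a range of control incidences and then used unchanged in the anlotinib arm.

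| Control incidence | λ per month | Anlotinib incidence | Excess (points) |
|---|---|---|---|
| 10% | 0.0084 | 12.2% | +2.2 |
| 20% | 0.0183 | 24.2% | +4.2 |
| 30% | 0.0303 | 35.8% | +5.8 |
| 50% | 0.0652 | 57.6% | +7.6 |

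The excess peaks at +7.7 points near λ = 0.08 and falls again for very common AEs (+2.3 at λ = 0.5). If the risk is confined to the first 2 months, it is 0.1 to 0.2 points.

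**4. Toxicity stops.** Let d be an extra stop hazard on anlotinib that also closes the AE window, so that μ becomes 0.0462 + d. The protocol gives no value for d.
- d = 0.01 (1 − exp(−0.12) = 11% stopped by 12 months): window 14.5 months, excess +1.2 to +4.0 points.
- d = 0.02 (21%): window 13.2 months, excess +0.3 to +0.9 points.

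If only anlotinib stops and gefitinib keeps the window open, the figures in step 3 stand at every stop rate.

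**5. What the added estimators would show.** With the window's end as a competing event, and no cut-off before month 18, the Aalen-Johansen value at t = 6 or 12 months is 1 − exp(−λ) × [μ + λ exp(−s(t − 1))]/s. Over the four incidences, with no extra stops, the gap at equal rates is +0.2 to +1.2 points at 6 months and +0.7 to +3.7 at 12 months.

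The 1-KM gap, censoring at the window's end, is zero if stopping is independent of the AE. In a simulation where a shared gamma frailty of variance 1 links the AE to the extra anlotinib stops (control incidence 30 and 50%), 1-KM was off by −0.3 to −1.1 points at 6 months and −0.8 to −2.5 at 12 months.

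**The case against.** **This is for the SAP.** Time-to-event and exposure displays are commonly left there, the list in section 13.2 is open-ended, and AE times are already collected. That is fair for the extra estimators taken alone. What remains is that the protocol itself names the measure and the comparison, ties the recording window to treatment, and leaves unclear which drug's last dose closes it. The last item governs data collection, and a later SAP cannot recover AEs that were not recorded.

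**The upper end is an edge case.** This stands. An excess near 8 points needs about 50% control incidence, a constant hazard and no dropout. Spreading the 20% dropout of section 3.3 over 18 months in both arms (an assumption) lowers +7.6 to about +6.6 at the same monthly rate. With 155 per arm, the standard error of a difference, √(2p(1 − p)/155), is 3.4, 4.5, 5.2 and 5.7 points at the four incidences, so the shift is about 0.65 to 1.34 standard errors.

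**The evidence of accumulation is thin.** It is five further patients of 21 on anlotinib alone, with no duration given for the whole-study column. Table 3 shows that accumulation is plausible; it does not supply a rate for this trial.

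**A stronger reading to avoid.** A reader might infer that the bias could equally run through zero and turn negative. Arithmetically, zero needs d = 0.0693 − 0.0462 = 0.0231 per month (24% extra stops by 12 months), and about −2 points at 50% incidence needs d = 0.03 (30%). All of those stops would have to end AE recording too. The documents support neither condition: no stop rate is given, sections 6.2 and 7.1 let patients go on with gefitinib after anlotinib intolerance, and the events that require leaving the study are a narrow set (arterial thrombosis, symptomatic grade IV venous thrombosis, confirmed leukoencephalopathy syndrome, gastrointestinal perforation).

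**Conclusion.** The point holds as a cheap improvement (COULD). If PFS behaves as section 3.3 assumes and monthly AE rates are equal, longer observation alone would raise crude incidence on anlotinib by about 2 to 8 points for accumulating AEs. This rests on exponential treatment times, constant equal AE hazards, control incidence of 10 to 50%, no dropout and no extra toxicity stops; it is an illustration, not a bound or a forecast. Toxicity stops that end the AE window would reduce the excess by an unknown amount. Anlotinib-only stops with gefitinib continued would not, provided gefitinib counts as study drug for the window.

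It does not follow that the crude tables are wrong or should go. They show what patients experienced. They cannot, on their own, separate toxicity from time observed. No decision rule uses them, so the effect is limited to interpretation.

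**What to change.** Keep the crude tables in section 13.2 and the synopsis, and add a short paragraph to section 13.2:

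- The AE window ends 30 days after the last dose of gefitinib or anlotinib/placebo, whichever is later. Use the same definition in section 9.2.
- For grade 3 or higher AEs, serious AEs and the AEs of special interest in section 7.2, estimate cumulative incidence of the first event by arm at 6 and 12 months with 95% CI (Aalen-Johansen; death and end of the AE window before the event are competing events; data cut-off is censoring).
- As a sensitivity analysis, give 1-KM censored at the end of the window.
- Show median exposure to each drug by arm beside the crude tables. Exposure-adjusted rates, if given, are descriptive only.

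The cost is one paragraph and a few tables; AE onset times and drug distribution and recovery are already recorded. The downside is that neither estimator fully removes the link between toxicity and stopping. Aalen-Johansen keeps up to about 4 points of the exposure gap at 12 months and about 1 point at 6 months, and 1-KM is biased if stopping depends on toxicity. The 6-month figure is the less affected one but misses later events, so both time points and both estimators should be shown.
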